| Statistical Analyses | 
The primary endpoints will be estimated as 95% confidence intervals using the Wilson score method. Due to the purely exploratory nature of all analyses and the fact that the four modules will be implemented in four separate daycare centers, the significance level will not be adjusted for multiple testing. The significance level will be set to 5% for all analyses. In a first step, descriptive analyses (frequency (percent), mean (SD) or median (IQR)) will be reported for all endpoints. For comparing the four groups with respect to some of the secondary endpoints, a chi-squared-test, ANOVA or Kruskal Wallis test will be used as appropriate. Subsequently, pairwise comparisons will be carried out using appropriate post-hoc tests. Analysis of the development of the psychosocial factors over time will be stratified by monitoring module and will use tests for repeated measurements such as the McNemar test, Repeated Measurements ANOVA and the Friedman test. In addition, baseline values and the follow-up values after 12 weeks will be compared between modules using appropriate tests such as the chi-squared test and ANOVA or non-parametric tests followed by post-hoc tests. Potential predictors of the rate of acceptance will be analysed (stratified by module) in univariable analyses using the chi-squared test and, if a sufficient sample size is obtained, additionally using multivariable logistic regression. If possible, an ICC value (intraclass correlation) for the daycare centers will be calculated as a basis for sample size estimation for a future cluster randomised study. All analyses will be performed in SAS, R or SPSS.
 |

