### **3 STUDY POPULATION**

#### **3.1 Selection of participating centers**

The study aims to include between 7 and 11 of the approximately 80 daycare centers located in the town of Würzburg for a study period of 12 weeks. For logistical reasons, larger daycare centers ( $\geq 50$  children) will be included preferentially. The selection of daycare centers will be carried out in cooperation with the office for youth, family and social affairs at Würzburg City Council using the following selection criteria:

...for the daycare centers in which modules 1 and 2 will be implemented:

- one daycare centre each, with a minimum of 100 children cared for at the centre and a minimum of 5 childcare workers
- consent of daycare centre's management to implementation of the study

...for the 1-3 daycare centers in which module 3 will be implemented:

- daycare centers with a minimum of 50 children of age  $\geq 2$  years cared for per centre (at least 175 children across all centers) and a minimum of 5 childcare workers per centre (at least 10 across all centers)
- consent of daycare centre's management to implementation of the study

... for the daycare centers in which module 4 will be implemented:

- between 4 and 6 daycare centers with a minimum of 250 children cared for and a minimum of 25 childcare workers across all centers
- consent of daycare centre's management to implementation of the study

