## 7 BIOMETRICAL ASPECTS

### 7.1 Endpoints

#### Primary endpoints for the different surveillance measures

- [Modules 1-3]: Rate of acceptance of the respective surveillance protocol defined as: proportion of children/childcare workers with “successful” participation in sample collection (mid-turbinate swab or saliva sample) among all children and childcare workers in the daycare centre. Parent/child groups and childcare workers who do not consent to participation in the study will be included in the calculations as “non-successful” participants. Each study participant will be classed as “successful” with respect to sample collection if at least 60% of all scheduled samples were collected successfully.

A surveillance protocol will be classed as “successful” if the rate of acceptance exceeds the following level:

≥30% (Module 1: intensive monitoring / mid-turbinate swabs)

≥37.5% (Module 2: extensive monitoring / mid-turbinate swabs)

≥37.5% (Module 3: intensive monitoring / saliva samples)

- [Module 4]:  
Proportion of cases with successful sample collection (i.e. completion of sample collection and diagnostic analysis – or receipt of test result in the case of external testing – within 72h after first telephone contact with hotline) among all cases of sample collection recommended for symptomatic children, symptomatic childcare workers or symptomatic household members of children/childcare workers

The surveillance protocol will be classed as “successful” if the rate of acceptance exceeds the following level:

≥70% (Module 4: symptom-based monitoring)

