#### Secondary endpoints for the different surveillance measures

- Comparison of initial rate of consent between the groups [Modules 1-4]
- Comparison of rate of acceptance between the groups [Modules 1-3]

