### **Exploratory analyses of potential predictors of acceptance**

- Association between initial consent / drop out regarding respiratory sample collection and:
  - age/ sex of child
  - family/household size
  - employment status, educational level
  - assigned screening module
  - personal assessment of the dangers of a SARS-CoV-2 infection
  - personal opinions on the necessity of social restrictions in response to SARS-CoV-2 infections
  - personal experience of SARS-CoV-2 (e.g. cases of disease or death in family or among friends and acquaintances)
  - personal opinions on child vaccinations

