## **7.2 Data analysis methods**

The primary endpoints will be estimated as 95% confidence intervals using the Wilson score method. Due to the purely exploratory nature of all analyses and the fact that the four modules will be implemented in separate daycare centers, the significance level will not be adjusted for multiple testing and all analysis results will be interpreted with the necessary caution. The significance level will be set to 5% for all analyses. In a first step, descriptive analyses

(frequency (percent), mean (SD) or median (IQR)) will be reported for all endpoints. The analysis of the secondary endpoints drop out rate, initial rate of consent, acceptance of blood sampling (stratified by childcare workers and parents), proportion of positive serological tests and proportion of positive PCR tests will, in a first step, compare all four groups using test procedures such as the Chi-squared-test, ANOVA or the Kruskal Wallis test as appropriate. Subsequently, pairwise comparisons will be carried out using appropriate post-hoc tests. The rate of acceptance will first be compared between all modules 1 to 3 using the chi-squared test. Analysis of the development of the psychosocial factors over time will be stratified by monitoring module and will use tests for repeated measurements such as the McNemar test, Repeated Measurements ANOVA and the Friedman test. In addition, baseline values and the follow-up values after 12 weeks will be compared between modules using appropriate tests such as the chi-squared test and ANOVA or non-parametric tests followed by post-hoc tests. Potential predictors of the rate of acceptance will be analysed (overall for all modules combined and stratified by module) in univariable analyses using the chi-squared test and, if a sufficient sample size is obtained, additionally using multivariable logistic regression. The analysis of costs, the proportion of absent days and data on the closure of daycare groups will be restricted to descriptive methods. The development of seroprevalence data over time will be reported using descriptive methods, possibly including graphical displays. The results of the children interviews will be reported descriptively using frequencies. If possible, an ICC value (intraclass correlation) for the daycare centers will be calculated as a basis for sample size estimation for a future cluster randomised study. All analyses will be performed in SAS, R or SPSS.

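### Modules 1 and 2 are one centre each and Module 3 is one to three, so the person-level tests between modules cannot tell a surveillance protocol effect from ordinary differences between centres

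*Protocol*

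**What the plan says.** The protocol's section 3.1 asks, for Modules 1 and 2, for "one daycare centre each, with a minimum of 100 children cared for at the centre and a minimum of 5 childcare workers". The Module 3 criteria there are "for the 1-3 daycare centers in which module 3 will be implemented". Section 7.1 defines acceptance person by person, as the "proportion of children/childcare workers with “successful” participation in sample collection (mid-turbinate swab or saliva sample) among all children and childcare workers in the daycare centre". Among the secondary endpoints it lists "Comparison of rate of acceptance between the groups [Modules 1-3", and among the exploratory predictors of acceptance "assigned screening module".

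Section 7.2 fixes the method: "The rate of acceptance will first be compared between all modules 1 to 3 using the chi-squared test". It also states: "The significance level will be set to 5% for all analyses". Drop-out, initial consent, acceptance of blood sampling, and positive serology and PCR proportions are compared across all four modules with chi-squared, ANOVA or Kruskal-Wallis tests and then pairwise. Psychosocial values at baseline and week 12 are also compared between modules. No centre term is stated for any of these, and no random assignment of centres to modules is described.

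One reason given for leaving the significance level unadjusted for multiple testing is, in the synopsis, that "the four modules will be implemented in four separate daycare centers". Section 7.2 gives the same reason without the number four; section 3.1 plans 7 to 11 centres.

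**The concern.** A module is given to whole centres, but the tests count persons. Acceptance in one centre reflects its management, staff, families and local infection situation as well as the sampling scheme. The protocol's own text makes independence between persons implausible:

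- Section 7.2 plans to estimate an ICC for centres, as input to a cluster-randomised successor.
- Section 4.1 points to interactions between children and between groups within a centre.
- Section 4.3.2 expects families with more than one participating child, and section 4.2 has the parents decide on sampling.

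Module 3 also excludes children under 2 years (section 3.3), so its population differs from that of Modules 1 and 2 whatever the protocol.

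Section 1.6 says the programmes are to be compared, and section 1.8 says the design makes that comparison possible. A p-value below 0.05 between Modules 1 and 2 would look like an effect of swabbing frequency, when it may only show that one centre had keener families.

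**Working it through.** **Inputs from the protocol.** Minimum numbers of persons are 105, 105 and 185 in Modules 1, 2 and 3 (section 7.5). Centres number 1, 1 and 1 to 3 (section 3.1). The level is 5% (section 7.2). Assumed acceptance is 30%, 37.5% and 37.5% (section 7.5).

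**Assumption.** The protocol gives no ICC (ρ). The range 0.005 to 0.05 is used here.

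**Step 1: how large the assumed centre differences are.** The between-centre SD is √(ρ·p·(1−p)), and the SD of the difference between two centres is √2 times that. With p = 0.375:

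| ICC | SD between centres | SD of difference between two centres |
|---|---|---|
| 0.01 | 4.8 points | 6.8 points |
| 0.02 | 6.8 points | 9.7 points |
| 0.05 | 10.8 points | 15.3 points |

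The whole gap that section 7.5 assumes between Modules 1 and 2 is 37.5 − 30 = 7.5 points. Centre differences of that order are therefore enough to create or hide it.

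**Step 2: Module 1 versus Module 2.** With one centre of 105 per module, the variance of each observed rate is multiplied by the design effect 1 + (105 − 1)·ρ, which the chi-squared test ignores. The true rejection rate with no module effect is roughly 2·[1 − Φ(1.96/√design effect)].

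| ICC | Design effect | 1.96/√design effect | Approximate rejection | Simulated rejection |
|---|---|---|---|---|
| 0 | 1 | 1.96 | 5% | 5% |
| 0.005 | 1.52 | 1.59 | 11% | 11% |
| 0.01 | 2.04 | 1.37 | 17% | 17% |
| 0.02 | 3.08 | 1.12 | 26% | 27% |
| 0.05 | 6.20 | 0.79 | 43% | 44% |

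**Step 3: the planned three-module test.** In the simulation every centre rate comes from one beta distribution with mean 37.5% and the given ICC, counts are binomial, and a Pearson chi-squared test with 2 degrees of freedom is applied at 5% (200,000 studies per setting). All modules are equally accepted, so every rejection is false.

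| ICC | Module 3 in 1 centre | 2 centres | 3 centres |
|---|---|---|---|
| 0 | 5% | 5% | 5% |
| 0.005 | 16% | 14% | 13% |
| 0.01 | 27% | 23% | 21% |
| 0.02 | 43% | 38% | 35% |
| 0.05 | 68% | 62% | 60% |

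The nominal 5% is reproduced only with no variation between centres. Using a common rate of 30% changes the results by about 0.2 points at most.

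**Step 4: can a centre-level test rescue the comparison?** For Module 1 versus 2, two centres minus two modules leaves 0 degrees of freedom for between-centre variation. Across Modules 1 to 3:

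- Module 3 in three centres: 5 − 3 = 2 degrees of freedom, critical F 19.0.
- Module 3 in two centres: 4 − 3 = 1 degree of freedom, critical F 199.5.
- Module 3 in one centre: none.

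The limit lies in the design, so no analysis plan can remove it.

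**The case against.** The comparison is secondary. Section 7.2 calls all analyses exploratory, promises careful interpretation, begins with descriptive reporting and plans an ICC. The primary result is each module's own rate with a Wilson interval, judged against its own threshold. Apart from clustering within families, the chi-squared test can answer whether these particular centres differ. For most other endpoints 7.2 names tests only as examples, so details may sit in an analysis plan not shown here. A pairwise acceptance test of Module 1 versus 2 is only implied.

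Much of this stands, and it limits the weight of the point. It does not remove it. The call for caution belongs to the sentence on multiple testing and mentions neither clustering nor confounding. The chi-squared test of acceptance is fixed in the protocol, and no later model can separate Module 1 from Module 2. The comparison is offered as one of protocols, not of named centres.

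Two stronger readings are not supported. A reader might infer that the success decisions fail; they use one threshold per module (section 7.1), so this defect does not touch them directly. A reader might also infer that a between-module p-value will decide which programmes go forward. Section 1.6 ties planning of the next study to the pre-defined success criteria and selection to acceptability and feasibility results, and no section links selection to such a p-value.

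**Conclusion.** The concern holds, limited to the between-module comparisons. As planned, these tests cannot attribute a difference to the surveillance protocol, and for Module 1 versus 2 nothing can. If centres vary with an ICC of 0.01 to 0.05, the nominal 5% test of acceptance would declare a module difference in 21 to 68% of studies in which the modules are equally accepted. Even an ICC of 0.005 gives 13 to 16%. These sizes rest on the assumed ICC range, beta-distributed centre rates and the minimum sample sizes. The inseparability of Modules 1 and 2 rests on no assumption.

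It should be corrected before analysis. It is not a fatal flaw, because the comparison is secondary and exploratory. Whether centre differences will in fact be presented as protocol effects cannot be known from the protocol; the plan permits it.

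**What to change.** In sections 7.1 and 7.2 and in the synopsis:

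1. Replace the between-module tests (acceptance, consent, drop-out, other secondary endpoints, baseline and week-12 values) with rates or summaries by centre and descriptive differences between modules.
2. State that module and centre are confounded, completely so in Modules 1 and 2, and that differences therefore cannot be attributed to the surveillance protocol.
3. Treat the assigned module in the predictor analysis in the same descriptive way.
4. Optionally, where both modules have at least two centres, give a centre-level comparison with its degrees of freedom stated. In practice this is Module 3 versus 4, for example on consent. With the centre numbers in section 3.1 that leaves between 2 + 4 − 2 = 4 and 3 + 6 − 2 = 7 degrees of freedom. It is unavailable if Module 3 runs in a single centre.

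While the synopsis sentence is being edited, its count of four centres should be reconciled with the 7 to 11 in section 3.1.

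The cost is wording, plus the loss of p-values that could not support a conclusion about the protocols. Drawing lots to assign centres to modules is not part of this fix: it would change the design and, with one centre per module, would still leave module and centre inseparable.

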#### **4.3.1 Monitoring programmes (SARS-COV-2)**

##### **4.3.1.1 Module 1: Intensive Monitoring – mid-turbinate swabs (1 centre, at least 100 children,**

2 mid-turbinate swabs per week)

All participating children and childcare workers in the selected daycare centre will be tested for SARS-CoV-2 with a mid-turbinate swab (cf. 6.4.1) twice a week (on Mondays and Thursdays). Test results will be available 24 hours after taking the swab. If a person is tested positive for SARS-CoV-2, the case module (4.3.1.8) will come into effect.

The monitoring programme will be continued for a period of 12 weeks.

4.3.1.2 Module 2: Extensive Monitoring – mid-turbinate swabs (1 centre, at least 100 children, 1 mid-turbinate swab per week)

All participating children and childcare workers in the selected daycare centre will be tested for SARS-CoV-2 with a mid-turbinate swab (cf. 6.4.1) once a week (on Wednesdays). Test results will be available 24 hours after taking the swab. If a person is tested positive for SARS-CoV-2, the case module (4.3.1.8) will come into effect.

The monitoring programme will be continued for a period of 12 weeks.

4.3.1.3 Module 3: Intensive Monitoring – saliva samples (1-3 centers, at least 175 children overall, 2 saliva samples per week)

All participating children and childcare workers in the selected daycare centers will be tested for SARS-CoV-2 using a saliva sample (cf. 6.4.2.) twice a week (on Tuesdays and Fridays). Test results will be available 24 hours after sampling. If a person is tested positive for SARS-CoV-2, the case module (4.3.1.8) will come into effect.

Children below the age of 2 years will not be included in the monitoring programme of module 3.

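### The combined-modules chi-squared analysis of acceptance predictors in 7.2 mixes persons with Module 4 test episodes and is not adjusted for module, so it can show associations that exist in no module

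*Protocol*

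**What the plan says.** - **Section 7.2** analyses predictors of the rate of acceptance "overall for all modules combined and stratified by module) in univariable analyses using the chi-squared test". It adds a regression conditionally: "if a sufficient sample size is obtained, additionally using multivariable logistic regression". It does not say which covariates enter.
- **Section 1.4 (Synopsis)** gives the same analysis without the combined part: "Potential predictors of the rate of acceptance will be analysed (stratified by module) in univariable analyses using the chi-squared test".
- **Section 7.1, primary endpoints**, defines two different rates. In Modules 1-3 the denominator is persons, "among all children and childcare workers in the daycare centre", and those who refuse consent count as unsuccessful. In Module 4 it is test episodes, "among all cases of sample collection recommended for symptomatic children, symptomatic childcare workers or symptomatic household members of children/childcare workers".
- **Section 7.1, secondary endpoints**, lists "Comparison of rate of acceptance between the groups [Modules 1-3"], and 7.2 likewise limits the between-module test of acceptance to Modules 1 to 3. The predictor analysis carries no such limit.
- **Section 7.1, predictors of acceptance**, names another outcome: "Association between initial consent / drop out regarding respiratory sample collection and" a list that includes age and sex of the child, household size, opinions and the assigned module.
- **Section 4.3.1.3** links age to module: "Children below the age of 2 years will not be included in the monitoring programme of module 3".

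**The concern.** A chi-squared test on one combined table cannot separate a predictor from the module. If acceptance differs between modules, and the predictor is also unevenly spread over them, the combined table shows an association even when none exists inside any module. The protocol itself assumes that acceptance differs (7.5), and its acceptance scale changes from persons to episodes in Module 4. A combined row would count a family that refused consent in Module 1 alongside a grandparent's swab arranged through the hotline in Module 4.

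Predictors of acceptance are research question III (1.7). Section 4.3.2 wants them in order to find targets for measures that raise acceptance. A spurious predictor, or one with the wrong sign, would misdirect that work. The decision to proceed to the follow-on study does not depend on it.

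**Working it through.** **Inputs from the protocol (7.5).** Minimum numbers are 105, 105 and 185 persons in Modules 1-3 and 279 expected episodes in Module 4. Assumed acceptance is 30%, 37.5%, 37.5% and 70%. The significance level is 5% (7.2).

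**The plan's own figure.** The Module 4 product is 3.5 × 275 × 0.025 × 12 = 288.75, whereas the protocol prints 279. That is a separate matter. Repeating the simulations below with 275, 279 or 289 episodes moved the results by about two percentage points at most, so 279 is kept.

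**Assumptions.** The protocol gives no age distribution. The share under 2 is set to 0 in Module 3 and varied elsewhere. There is no age effect in any module, and observations are taken as independent.
- Set A: the same share (10-35%) in Modules 1, 2 and 4, as might happen if each episode is attributed to the family's index child.
- Set B: 15-35% in Modules 1-2 but 5% of Module 4 episodes, as might happen if age is that of the person tested, since many would be adults.

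**Expected gap, by hand.**

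Set A at 20%:
- Under 2: (21 × 0.30 + 21 × 0.375 + 55.8 × 0.70) / 97.8 = 53.235 / 97.8 = 54.4%.
- Others: (84 × 0.30 + 84 × 0.375 + 185 × 0.375 + 223.2 × 0.70) / 576.2 = 282.315 / 576.2 = 49.0%.
- Spurious gap: +5.4 points.

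Set B at 35% and 5%:
- Under 2: (36.75 × 0.30 + 36.75 × 0.375 + 13.95 × 0.70) / 87.45 = 34.57 / 87.45 = 39.5%.
- Others: (68.25 × 0.30 + 68.25 × 0.375 + 185 × 0.375 + 265.05 × 0.70) / 586.55 = 300.98 / 586.55 = 51.3%.
- Spurious gap: −11.8 points, the opposite sign.

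Modules 1-3 only at 20%: 14.175 / 42 = 33.8% against 126.075 / 353 = 35.7%, a gap of −2.0 points.

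**Rejection rates.** There were 40,000 simulated trials per scenario. The pooled statistic is N(ad − bc)² / [(a+b)(c+d)(a+c)(b+d)]. The Cochran-Mantel-Haenszel statistic is [Σ(aᵢ − xᵢmᵢ/nᵢ)]² / Σ[xᵢ(nᵢ−xᵢ)mᵢ(nᵢ−mᵢ) / (nᵢ²(nᵢ−1))], where xᵢ is the number with the predictor and mᵢ the number of successes in module i. Both are compared with 3.84.

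| Scenario (no true effect) | Gap, points | Pooled | Stratified |
|---|---|---|---|
| Set A, 10% | +5.0 | 10% | 5% |
| Set A, 20% | +5.4 | 17% | 5% |
| Set A, 35% | +6.2 | 29% | 5% |
| Set B, 15% | −5.3 | 10% | 5% |
| Set B, 25% | −9.3 | 31% | 5% |
| Set B, 35% | −11.8 | 54% | 5% |
| Modules 1-3 only, 10-35% | −1.9 to −2.2 | 5-6% | 5% |

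The 10-54% range describes these two sets and is not a bound. With 25% under 2 in Modules 1-2 and 15% of Module 4 episodes, the distortions cancel (49.8% against 49.8%) and the pooled test rejects in 5%. With 15% and 35% the gap is +14.1 points and it rejects in 82%.

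**Another predictor.** For a binary predictor at 30% in Modules 1-3 and 30%, 40% or 50% in Module 4, the pooled test rejects in 5%, 15% and 43%. With equal acceptance in all modules it stays at 5% even when age is unbalanced.

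**The case against.** The best defence is that the safeguard sits in the same sentence. The module-stratified results will be reported beside the combined one, so a combined signal absent from every module would be visible. A regression is planned if numbers allow, and the assigned module is a listed predictor, which can only be studied in combined data. All analyses are labelled exploratory and are to be read with caution. Section 8 also refers to a statistical analysis plan, not at hand, that may settle details.

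Much of this stands, and it lowers the weight of the point. It does not repair the pooled test. No rule says which result prevails when the two disagree. The regression is conditional, and module is not named in it. Exploratory status explains the lack of multiplicity control but does not remove confounding.

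A second defence is that 7.1 names initial consent or drop out as the predictor outcome. Consent is given per person and is compared over Modules 1-4, so on that reading no units are mixed and the 70% rate does not apply. That is a fair reading of 7.1. Section 7.2, however, names the rate of acceptance, so the two sections disagree and must be reconciled.

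A reader might also infer that the exclusion of under-2s from Module 3 is enough to distort the analysis. At the protocol's rates it is not: within Modules 1-3 the pooled test rejects in 5-6%. Rates of 14-31% or about 30-65% (15-35% under 2 in Modules 1-2) need Module 3 acceptance of 50% or 60%, and the protocol assumes 37.5%.

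**Conclusion.** The point holds in a limited form. The combined analysis in 7.2 is unadjusted, mixes persons with episodes if the outcome is the rate of acceptance, and is absent from the synopsis. At the protocol's own rates the pooled test of age under 2 rejects in about 10-54% of null trials over the two sets of age shares, against about 5% when stratified, and the sign of the spurious gap depends on the assumed share. The driver is Module 4.

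The size rests on assumed age shares, on 7.2's outcome being the one meant, and on independent observations. It would be wrong to conclude that module differences must appear as predictor effects: a predictor balanced over modules is not distorted. It would also be wrong to treat the pooled test as the only planned analysis. The pre-set success criteria are unaffected.

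**What to change.** 1. In 7.2, limit the combined analysis of the rate of acceptance to Modules 1-3. Use a Cochran-Mantel-Haenszel test stratified by module, or logistic regression with module as a fixed effect, in place of the pooled chi-squared test.
2. Analyse predictors of Module 4 test completion separately, by episode.
3. Where the outcome is initial consent or drop out, counted per person, Module 4 may stay in the combined analysis, provided that it is stratified or adjusted by module.
4. Reconcile the synopsis, the predictor list in 7.1 and section 7.2 on the outcome and on whether modules are combined.

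The cost is wording only, since module is known for every participant. Stratifying by module does not remove differences between centres within Modules 3 and 4, which may have several centres each, and the report should say so.
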